## Study outcomes

### Primary outcome

Monthly prevalence of rapid diagnostic test (RDT)-confirmed malaria infections among women at ANC1 (asymptomatic and symptomatic).Correlation at health facility and district level between malaria prevalence at the ANC1 (monthly or quarterly) and among children tested during cross-sectional household surveys.

### Secondary outcomes

Comparison of ANC1 data to cross-sectional household survey data to ascertain whether pregnant women attending ANC1 can be a sentinel population for estimating, both overall and by gravidity:Bed net ownership and use the previous night.Population access to bed nets (proportion of households achieving one net for every two people).Care-seeking behaviour for malaria.Reported acceptability and feasibility of ANC1 malaria surveillance to women and providers.Relationship between ANC1 malaria prevalence and malaria case incidence derived from DHIS2 (where population denominator data are available).

## Methods

### Study design

This is a multi-country, observational, serial cross-sectional study with data from pregnant women attending ANC1 aggregated monthly. These data will be compared to similar survey questions (adapted from standard demographic health survey and malaria indicator survey questions) administered to households as part of cross-sectional surveys being conducted for evaluation of a number of different interventions (ClinicalTrials.gov Identifier: NCT04716387, NCT04157894, NCT04148690). Malaria prevalence by RDT among children under 5 years of age collected during the household surveys will also be compared to the prevalence among pregnant women at ANC1 in the same or a similar time period.

### Study population

All pregnant women of legal age and emancipated minors attending ANC1 at selected health facilities in Benin, Burkina Faso, Mozambique, Nigeria, Tanzania, and Zambia are approached for enrollment (Table 1). In Mozambique and Nigeria only, pregnant women below the legal age are considered eligible with the consent of a legal guardian. Pregnant women with symptoms of severe disease as determined by the clinician at the ANC clinic are excluded and referred for urgent case management. Children under 5 years of age whose parents respond to the cross-sectional household survey and provide consent for malaria testing of their children are also included.

**Table 1 Tab1:** Study site, participant, and survey details

Country	Study location	Number of study health facilities collecting ANC1 data	Age of women enrolled (years)	Study collecting cross-sectional household survey data	Methodology for identification of target health facility (HF) catchments	Sample size for cross-sectional household survey
Benin	Atlantique Department	40	15–49	Group Antenatal Care study	HFs with 30–120 first ANC visits per month that were easily accessible throughout majority of the year were selected, catchment areas were identified with the assistance of the HF staff	2,520 (of which 1,320 were selected from women with a completed pregnancy in the past year), twice
Burkina Faso	Banfora District	7	20–49	New Nets Project	HFs with > 20 first ANC visits per month on average in DHIS2 from 2017	190, annually
	Gaoua District	7				190, annually
	Orodara District	7				190, annually
Mozambique	Changara District	7	18–49	New Nets Project	HFs with > 20 first ANC visits per month on average in DHIS2 from 2017 – 2019	420, annually
	Guro District	7				420, annually
	Chemba District	7				420, annually
Nigeria	Asa local government area	10	18–49	New Nets Project	By LGA, ten HFs with the most first ANC visits per month reported in DHIS2 in 2019	420, annually
	Ejigbo local government area	10				420, annually
	Ife North local government area	10				420, annually
	Moro local government area	10	14–49			420, annually
Tanzania	Geita Region	40	15–49	Group Antenatal Care study	HFs with 30–120 first ANC visits per month that were easily accessible throughout majority of the year were selected, catchment areas were identified with the assistance of the HF staff	2,320 (1,120 were selected from women with a completed pregnancy in the past year), twice
Zambia	Chadiza District	21	15–49	Proactive community case management	All HFs in the district were included and catchment area boundaries were defined by the Ministry of Health	2178, twice

### Study settings and location

This study is leveraging several planned intervention studies, including cross-sectional household surveys (modified malaria indicator surveys) at the district or village level that collect parasite prevalence data among children under 5 years (and other age groups as well, depending on country-specific epidemiology and national malaria control programme priorities). In Burkina Faso, Mozambique, and Nigeria, study activities are aligned with surveys from the New Nets Project, an observational quasi-experimental study that is evaluating the cost-effectiveness of various types of insecticide-treated nets [16]. During the New Nets Project, annual cross-sectional surveys are conducted from 2019 to 2022, including assessments of malaria prevalence, and corresponding ANC1-based surveillance occurs in a subset of health facilities in corresponding districts. Additionally, studies assessing the impact of group ANC are planned in the catchment areas of 40 health facilities each in Geita Region, Tanzania, and Atlantique Department, Benin, with corresponding cross-sectional surveys occurring as the primary method of evaluating the impact of the group ANC intervention. Due to the COVID-19 pandemic, the group intervention was stopped early in Tanzania, but the ANC1-based surveillance assessment and cross-sectional surveys continue. Cross-sectional surveys are conducted at study baseline and endline (November 2019 and June 2021 in Tanzania, February/March 2021 and September/October 2022 in Benin). In Chadiza, Zambia, this ANC1-based surveillance pilot leverages a study assessing the impact of proactive community case management in 21 health facility catchments, with surveys conducted in May 2021 and May 2023.

### Health facility selection

Health facilities and their catchment areas are selected for participation in the parent studies according to the needs of each study; of these, health facilities with a minimum of 20 ANC1 per month are selected for co-inclusion in this ANC surveillance pilot. In some studies, all eligible health facilities are included, while in others a subset of eligible facilities are randomly selected for inclusion. Two activities are integrated into routine ANC1 consultations: malaria testing of eligible participants regardless of symptoms using an RDT, and administration of a questionnaire to collect data on participant demographics, gravidity, insecticide-treated net ownership and use, and care-seeking behaviour. For each facility, the corresponding catchment villages were identified in collaboration with the health facility workers. From among all the villages in the health facility catchment area, 1–2 villages or enumeration areas were selected for household sampling for the cross-sectional survey proportional to population size. The selected areas were mapped and respondents randomly selected as indicated by the parent study conducting the cross sectional survey.

### ANC1 screening and enrollment

All pregnant women attending ANC1 are tested for malaria infection. During group counselling sessions at initial ANC1 intake, women are informed of this pilot surveillance activity. Women are consented for this pilot surveillance activity individually prior to testing. The number of women refusing malaria testing is noted on a screening form. For consenting women, a malaria RDT is administered concurrently with other routine ANC testing, using blood from the same finger prick. While awaiting the results from these tests, the short ANC surveillance questionnaire (Additional file 1) is administered by a trained study team or staff member, and the RDT result recorded when available. Women have the option of responding to the questionnaire even if they declined the RDT. During a regular ANC visit, the nurse asks questions to determine a woman’s age, gravidity, and gestational age. These data are recorded in the ANC registers and copied into the corresponding study questionnaires to avoid asking women the same questions twice. In Burkina Faso, Mozambique, and Zambia, a paid trained field worker assists with recruitment and administering the questionnaire while in the other countries, this task is completed by clinic staff.

### Blood sample collection

As stated above, finger-prick capillary blood samples are collected for malaria diagnosis using malaria RDTs. The RDT used for both ANC1 surveillance and the cross-sectional household surveys is determined by national procurement protocols. For ANC1 surveillance, the blood used for malaria testing is taken from the same finger prick that is used to collect blood for standard ANC testing. If positive, treatment is given to the women according to the national guidelines for malaria treatment.

### Sample size

A sample size of 88 people from a population of 1,000 people produces a two-sided 95% confidence interval with a precision (half-width) of 0.10 when the actual proportion is near 0.50. The sample size needed for a given confidence interval around a proportion is greatest for a proportion of 0.50. This is used to provide the most conservative assumption of sample size. The health facility sampling scheme is implemented across the different countries to provide a minimum of 88 women enrolled per month per sampling unit (i.e., health facility, district, or country), for a yearly total of 1,056 women per sampling unit. In cases where this sample size is not achieved in a single month at a given health facility, the data will be aggregated across facilities to provide a district/country estimate or across months to provide quarterly estimates to have sufficient sample size to provide an accurate estimate.

To calculate the correlation between the facility-level data and community-level data, an estimated minimum of 20 facilities is needed to provide an accurate estimate of the correlation coefficient (R), using a two-tailed alpha test (alpha 0.05) and with 80% power, assuming an expected correlation coefficient of 0.6 or greater (Fig. 1). This is not feasible across all individual countries, thus using the combined data from multiple countries aimed to ensure sufficient sample sizes to assess the correlation.

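### The ±0.10 precision claimed for 88 women rests on a fixed population of 1,000, and the quarterly fallback does not reach 88 at the plan's own 20-visit facility floor

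*Protocol article*

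**What the plan says.** The precision claim is in the Sample size section: "A sample size of 88 people from a population of 1,000 people produces a two-sided 95% confidence interval with a precision (half-width) of 0.10", for a true proportion near 0.50, which the section describes as the most conservative choice. The figure is then made a monthly target: "The health facility sampling scheme is implemented across the different countries to provide a minimum of 88 women enrolled per month per sampling unit". The sampling unit is defined as a health facility, a district or a country, and the yearly total is given as 1,056 women per unit.

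If a facility falls short in a month, "the data will be aggregated across facilities to provide a district/country estimate or across months to provide quarterly estimates", and the section presents this as giving enough women for an accurate estimate.

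Facility volume is set elsewhere. The Health facility selection section says that "health facilities with a minimum of 20 ANC1 per month are selected for co-inclusion in this ANC surveillance pilot". Table 1 gives country criteria:
- Burkina Faso and Mozambique: more than 20 first visits a month on average, seven facilities per district.
- Benin and Tanzania: 30 to 120 a month.
- Nigeria: the ten busiest facilities in each area.
- Zambia: "All HFs in the district were included and catchment area boundaries were defined by the Ministry of Health", with no volume stated.

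The Primary outcome section includes a correlation at facility as well as district level, using monthly or quarterly ANC1 prevalence.

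**The concern.** This is the only precision statement for the first primary outcome, monthly prevalence at ANC1, and three features of it do not fit the design.

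First, a single population of 1,000 is used for units as different as one clinic and a whole country. All eligible attenders are approached, so the women are not a sample from a list of 1,000, and the section's own yearly total of 1,056 exceeds that population.

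Second, pooling over a quarter is offered as the remedy for small facilities, yet the admission floor is too low for it to work at facilities near that floor. These facilities contribute to the facility-level correlation in the primary outcome.

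Third, the other remedy, pooling across facilities, carries no allowance for prevalence differing between facilities, although a facility-level correlation presupposes such differences.

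At stake is whether readers and programmes can rely on ±0.10 when judging month-to-month or facility-to-facility differences.

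**Working it through.** **Inputs from the Sample size section:** n = 88, N = 1,000, half-width d = 0.10, p = 0.50, two-sided 95% (z = 1.96). **From Health facility selection and Table 1:** floor of 20 visits a month; seven facilities per district in Burkina Faso and Mozambique. **Assumed, because the documents give none:** intracluster correlation (ICC) of 0.02, 0.05 and 0.10.

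**1. The plan's figure.**
- Uncorrected: n0 = z²p(1−p)/d² = 1.96² × 0.25 / 0.01 = 96.04, so 97 women.
- Corrected: n = n0 / (1 + (n0 − 1)/N) = 96.04 / (1 + 95.04/1,000) = 87.7, so 88. The stated figure reproduces, with a design effect of 1.
- The result moves with N: 80.7 (81 women) at N = 500 and 95.1 (96 women) at N = 10,000.
- 88 women without the correction: 1.96 × √(0.25/88) = 0.1045.

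**2. One facility at the floor.**
- Month: n = 20, half-width 1.96 × √(0.25/20) = 0.219.
- Quarter: n = 3 × 20 = 60, below 88; half-width 1.96 × √(0.25/60) = 0.127. Keeping the N = 1,000 correction still gives 0.123.
- Volume needed for 88 in a quarter: 88/3 = 29.3, so 30 a month. At 20 a month, 88 takes 88/20 = 4.4 months.
- If p = 0.20 is assumed: 1.96 × √(0.16/60) = 0.101.
- Sixty counts visits, before refusals and age exclusions (Burkina Faso enrols ages 20 to 49 only).
- The comparison with the household survey uses a three-month window (Data analysis and modelling), so the same 60 applies there.
- Benin and Tanzania: 3 × 30 = 90 visits at their lower limit, which reaches 88 before refusals.

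**3. Seven facilities at the floor, pooled for one month.**
- n = 7 × 20 = 140. Under simple random sampling: 1.96 × √(0.25/140) = 0.083.
- With design effect DEFF = 1 + (20 − 1) × ICC, half-width = 1.96 × √(0.25 × DEFF/140):

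| Assumed ICC | DEFF | Half-width |
|---|---|---|
| 0.02 | 1.38 | 0.097 |
| 0.05 | 1.95 | 0.116 |
| 0.10 | 2.90 | 0.141 |

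- With the number of facilities fixed at seven, the n giving 0.10 solves n = 96.04 × [1 + (n/7 − 1) × ICC]. At ICC 0.05: n = 91.24 + 0.686n, so n = 91.24/0.314, about 291. At ICC 0.10 no n suffices, because the half-width cannot fall below 1.96 × √(0.25 × 0.10/7) = 0.117.

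**The case against.** The population of 1,000 is stated openly and the arithmetic is right, so a reader who infers that 88 is a miscalculation would be wrong. Removing the correction costs only 0.0045 in half-width. This stands, and it makes the correction the minor part of the point.

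The quarterly shortfall is also narrower than it first looks. Benin and Tanzania account for 80 of the 183 facilities in Table 1 and meet the needed volume; Nigeria's 40 are the busiest in their areas. The criterion of more than 20 governs the 42 facilities in Burkina Faso and Mozambique, and Zambia's volumes are not given. The plan sets 88 per sampling unit and does not promise it at every facility, and pooling a district does exceed 88. All of this stands. But district pooling gives up the facility-level value that the primary correlation uses, and the quarterly route is still offered as adequate.

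The design-effect figures rest on assumed ICCs, and at 0.02 the 140 women meet 0.10 even at p = 0.50. Where every facility in a district is enrolled, as Table 1 says for Zambia, there is no facility-sampling stage to allow for. The allowance matters where facilities are a subset: Study settings and location says this of the New Nets Project districts, and Health facility selection says that some studies choose facilities at random. For Nigeria's purposive choice the formula is only an approximation.

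Two further inferences are tempting. One is that 88 acts as a cut-off that removes small facilities from the correlation. The text describes aggregation and states no exclusion. The other is that published intervals will be too narrow. No section says how reported intervals will be computed, and the ANC1-to-community relationship is to be modelled by mixed-effects logistic regression with adjustment for sampling effort. Interval methods may properly be left to a fuller document.

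**Conclusion.** The concern holds, at moderate severity. The stated ±0.10 is not delivered at every level to which the plan applies it.

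The firmest part needs no outside assumption about clustering: at the plan's own floor a facility-quarter holds at most 60 women, against a target of 88, with a half-width of 0.127 at the plan's own p of 0.50. It is shown for facilities near the floor, which the Burkina Faso and Mozambique criterion allows, and possibly for Zambia. It is not shown for Benin or Tanzania. If prevalence is nearer 0.20, the floor quarter gives about ±0.10, so the practical loss depends on a prevalence that the documents do not state.

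The single N of 1,000 is unjustified but costs little. The missing design effect matters only for pooled estimates from a subset of facilities, and its size (0.097 to 0.141 for 140 women) depends on the assumed ICC. No hypothesis test rests on 88, so this is a matter of correcting a precision claim rather than of an invalid analysis.

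**What to change.** In the Sample size section:

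1. Drop the population of 1,000.
2. Restate the expected 95% half-width by level at p = 0.50: facility-month and facility-quarter at the floor of 20 visits (0.219 and 0.127, before refusals and exclusions), and district-month over a stated ICC range where the facilities are a subset of the district. A lower assumed prevalence can be shown beside these.
3. State that 88 is a precision target, and that every facility enters the facility-level correlation with its numerator and denominator.

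This needs no additional women and no change to facility selection. The cost is a short rewrite and stated figures that look less favourable than ±0.10.

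### The 20-facility minimum is a test of zero correlation and not a basis for an accurate R; the district-level correlation has no calculation, and a raw facility-level R is biased low

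*Protocol article*

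**What the plan says.** The Sample size section states that "an estimated minimum of 20 facilities is needed to provide an accurate estimate of the correlation coefficient (R"). As the basis it names a two-sided test at the 5% level, power of 80%, and an effect size given as follows: "assuming an expected correlation coefficient of 0.6 or greater (Fig. 1"). No null value, target interval width or allowance for sampling error in either prevalence appears. On pooling, the section explains that "using the combined data from multiple countries aimed to ensure sufficient sample sizes to assess the correlation".

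The primary outcome covers two levels: "Correlation at health facility and district level between malaria prevalence at the ANC1 (monthly or quarterly"). The sample size text treats only the facility level.

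Table 1 gives the number of facilities and the household survey size for each location. Under Health facility selection, one or two "villages or enumeration areas were selected for household sampling for the cross-sectional survey proportional to population size" in each facility catchment. Under Objectives, the purpose of the correlation is to validate ANC1 surveillance as representative of the prevalence that household surveys report.

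**The concern.** Power to reject zero and accuracy of an estimate are different properties. A number of units that suffices for the first can leave the correlation almost unknown. With 20 units, an observed R of 0.44 (about 20% of variance) is already significant at the two-sided 5% level. For a validation study the reader needs to know how closely R will be estimated. The same section does use a precision criterion for prevalence (88 women for a half-width of 0.10), but not for the correlation.

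Two further gaps follow. The district-level correlation is primary but has no sample size basis. And the calculation does not say whether 0.6 is the correlation between true prevalences or between measured ones. If it is the former, small samples per catchment would make a good surrogate look weaker than it is, and adding facilities does not remove that bias.

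**Working it through.** **1. The plan's figure.** Inputs from Sample size: two-sided alpha 0.05, power 80%, R = 0.6. The null of zero is inferred because it reproduces the result.

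n = ((z₀.₉₇₅ + z₀.₈₀) / atanh 0.6)² + 3 = ((1.960 + 0.842) / 0.693)² + 3 = 19.3, rounded up to 20. The arithmetic is correct. Power at n = 20 is 81.5%.

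**2. Precision at R = 0.6.** 95% CI = tanh(0.693 ± 1.96/√(n − 3)), units treated as independent.

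| Units | 95% CI |
|---|---|
| 13 (locations in Table 1) | 0.07 to 0.87 |
| 20 (stated minimum) | 0.21 to 0.82 |
| 61 (one third of 183, an illustrative allowance for clustering) | 0.41 to 0.74 |
| 183 (all facilities in Table 1) | 0.50 to 0.69 |

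Half-widths of 0.20, 0.15 and 0.10 need 43, 74 and 161 units.

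**3. Planned facilities.** Table 1: Benin 40, Burkina Faso 3 × 7 = 21, Mozambique 3 × 7 = 21, Nigeria 4 × 10 = 40, Tanzania 40, Zambia 21. Total 183. The smallest correlation detectable with 80% power at 183 independent facilities is 0.21.

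**4. District level.** Table 1 has 1 + 3 + 3 + 4 + 1 + 1 = 13 locations, two of which are a region and a department. For one survey round, power at 0.6 = Φ(0.693 × √10 − 1.96) = Φ(0.23) = 59%. The correlation detectable with 80% power is 0.71. Repeat surveys add pairs: with an assumed 3 to 4 annual rounds in the 10 New Nets Project locations and two rounds in the other three, 10 × 3 + 6 = 36 to 10 × 4 + 6 = 46. These are correlated within location, so the effective number lies between 13 and 36–46. If 36 pairs were independent, power would be 98%.

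**5. Sampling error at facility level.** Survey subjects per catchment, if spread evenly: Burkina Faso 190/7 = 27, Nigeria 420/10 = 42, Tanzania 2,320/40 = 58, Mozambique 420/7 = 60, Benin 2,520/40 = 63, Zambia 2,178/21 = 104. How many are children with an RDT is not stated.

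Observed R = true R × √(reliability of survey × reliability of ANC1), where reliability = SD² / (SD² + DE × p(1 − p)/m). Here m is the number sampled per facility and DE the design effect, applied to the survey side only. The documents do not give p, SD or DE. Assumed: mean prevalence 0.30, between-facility SD 0.10 to 0.20, DE 1 to 1.5, and 60 to 180 ANC1 women in the three-month window (60 is the 20-per-month floor times three).

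- Low end (SD 0.10, DE 1.5, 27 surveyed, 60 women): survey 0.01/(0.01 + 0.0117) = 0.46; ANC1 0.01/(0.01 + 0.0035) = 0.74; observed R = 0.6 × √(0.46 × 0.74) = 0.35.
- High end (SD 0.20, DE 1, 104 surveyed, 180 women): survey 0.04/(0.04 + 0.0020) = 0.95; ANC1 0.04/(0.04 + 0.0012) = 0.97; observed R = 0.6 × √(0.95 × 0.97) = 0.58.

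Even at 0.35, power against zero is above 99% with 183 independent facilities and about 80% with an effective 61. It fell below 80% at 183 only in some scenarios with SD 0.05, the lowest being 40% (prevalence 0.50, DE 2, 27 surveyed, 60 women).

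**The case against.** The strongest reply is that nobody plans a 20-facility study. Twenty is a minimum, countries are to be pooled, and Table 1 lists 183 facilities, for which the CI would be about 0.50 to 0.69 if they were independent. That stands. A reader might infer that the study has lost its 80% power; for the pooled facility-level test the documents do not support this.

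A reader might also say that 13 locations breach the plan's own minimum of 20. They do not, because that minimum was set for facilities, and repeat surveys supply more than 13 district-level pairs. The 59% and the CI of 0.07 to 0.87 describe one round only. What stands is that a level named in the primary outcome has no calculation.

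The attenuation figures depend on a prevalence, SD and design effect that the documents do not give, and on reading 0.6 as the error-free correlation. If 0.6 is the correlation expected between measured prevalences, attenuation is already included. The direction of the bias is certain; its size is not.

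Finally, nothing says that a significant R would by itself count as validation. The Data analysis section also plans mixed-effects logistic regression adjusting for sampling effort, leave-one-out cross-validation by district, and Kendall rank correlation. These may deal with part of the sampling error. They do not change what the article says 20 facilities provide, nor correct a raw R reported as the primary outcome.

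**Conclusion.** The concern holds in this limited form. The number 20 is computed correctly, but the property claimed for it is wrong: it is the size needed to detect 0.6 against zero, and at R = 0.6 it leaves a 95% CI of 0.21 to 0.82. This rests only on the plan's own inputs.

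The district-level correlation is primary without a sample size basis. With 13 locations, one round gives 59% power and a CI of 0.07 to 0.87. Repeat rounds improve on this by an amount that depends on the unstated within-location correlation.

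A raw facility-level correlation is biased towards zero at any number of facilities. Under the assumed inputs a true 0.6 would be seen as about 0.35 to 0.58. This is conditional on those inputs, on an even spread of survey subjects, and on 0.6 being the correlation before sampling error. It is a matter of interpretation and reporting, and no reason to doubt that the pooled analysis can reject zero under most assumptions.

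**What to change.** 1. Reword the sample size text: 20 facilities give 80% power to detect a correlation of 0.6 against zero (two-sided alpha 0.05). Drop the claim of accuracy.
2. State the expected 95% CI for R at the planned number of facilities and at the planned number of district-level pairs, allowing for clustering by country and for repeat surveys in the same location.
3. Say whether 0.6 is the correlation before or after sampling error in the two prevalences.
4. Beside the raw R, report a correlation corrected for binomial sampling error in both measures, with its interval. A bivariate binomial random-effects model of the ANC1 and survey counts per facility would do this, with the survey's clustering in one or two villages taken into account.

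The primary status of the district-level correlation need not change. The cost is a revised paragraph and one further model on counts that are already collected. The stated figure will look less favourable.

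### The stated reason for combining countries in the facility correlation conflicts with Table 1, where all six countries meet the 20-facility minimum, and no country term is named to keep between-country differences out of the result

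*Protocol article*

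**What the plan says.** In the protocol article, one of the primary outcomes is the correlation between malaria prevalence at ANC1 and among surveyed children, at facility and at district level (Study outcomes).

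The Sample size section plans the facility-level correlation "using a two-tailed alpha test (alpha 0.05) and with 80% power", "assuming an expected correlation coefficient of 0.6 or greater", and arrives at a minimum of 20 facilities. The next sentence reads "This is not feasible across all individual countries, thus using the combined data from multiple countries aimed to ensure sufficient sample sizes". No other reason for combining countries is given there.

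Table 1 (Study population) has a column headed "Number of study health facilities collecting ANC1 data". Study settings and location confirms three of the six country totals: "catchment areas of 40 health facilities each in Geita Region, Tanzania, and Atlantique Department, Benin" and, for Zambia, "proactive community case management in 21 health facility catchments".

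Data analysis and modelling adds a mixed-effects logistic regression that allows for age, gravidity, transmission intensity and season and adjusts for sampling effort. It also adds leave-one-out cross-validation by district and a Kendall coefficient for district ranking. Country is not named as a stratum or an effect in any of these.

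**The concern.** The minimum and the facility counts stand in the same article and do not agree. If every country has at least 20 facilities, the only stated reason for combining countries fails.

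Combining is not neutral. A correlation over facilities from six countries mixes two questions: whether countries with high ANC1 prevalence have high child prevalence, and whether facilities with high ANC1 prevalence do so inside a country. The uses that the article promotes (finding hot spots, subnational modelling, local targeting, ranking districts) depend on the second. Country-level features can move both measures together. For example, the article says that the rapid test used in both settings follows national procurement, and survey months differ by country. Any distortion from this source would tend to favour the validation claim.

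**Working it through.** **1. The plan's own figure.** Inputs from Sample size: r = 0.6, two-sided alpha 0.05, power 80%. The null of zero is implied. By Fisher's z:

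n = ((1.960 + 0.842) / atanh(0.6))² + 3 = (2.802 / 0.6931)² + 3 = 19.34, rounded up to 20.

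The stated 20 is reproduced. A one-sided test would give 15.87, so the two-sided reading is the one that fits.

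**2. Facilities per country, from Table 1.** Power = Φ(atanh(0.6) × √(n − 3) − 1.960).

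| Country | Facilities | Power at r = 0.6 |
|---|---|---|
| Benin | 40 | 98.8% |
| Burkina Faso | 3 × 7 = 21 | 83.7% |
| Mozambique | 3 × 7 = 21 | 83.7% |
| Nigeria | 4 × 10 = 40 | 98.8% |
| Tanzania | 40 | 98.8% |
| Zambia | 21 | 83.7% |
| Total | 183 | |

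All six reach 20. The infeasibility statement would be true of single districts or local government areas: the same formula gives 28% power with 7 facilities and 45% with 10.

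**3. What combining without a country term can do.** With 183 facilities, r is significant above 0.145. The protocol does not give the share of facility-level variance that lies between countries (ICC), so a range was assumed. The simulation used the Table 1 counts, within-country correlation of exactly zero, the same ICC for both measures, and 4,000 replicates per row. In large samples, pooled r = ICC × between-country correlation.

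| Between-country correlation | ICC | Median pooled r | Pooled test significant | Pooled r ≥ 0.6 |
|---|---|---|---|---|
| 0.7 | 0.2 | 0.11 | 38% | 0% |
| 0.7 | 0.5 | 0.29 | 78% | 3% |
| 0.7 | 0.7 | 0.44 | 89% | 22% |
| 0.9 | 0.2 | 0.14 | 47% | 0% |
| 0.9 | 0.5 | 0.37 | 91% | 7% |
| 0.9 | 0.7 | 0.57 | 97% | 41% |
| 0.9 | 0.8 | 0.66 | 98% | 63% |
| 1.0 | 0.5 | 0.42 | 94% | 13% |
| 1.0 | 0.7 | 0.62 | 99% | 55% |

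A correlation computed after centring each facility on its country mean was significant in 4.4% to 5.7% of replicates over all settings run, close to the nominal 5%.

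**4. Precision of within-country estimates.** 95% intervals around r = 0.6 are tanh(0.6931 ± 1.96/√(n − 3)):

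- 21 facilities: 0.23 to 0.82
- 40 facilities: 0.36 to 0.77
- crude pool of 183: 0.50 to 0.69
- Fisher-z combination of the six countries, assuming a common r: the weights sum to 183 − 6 × 3 = 165, so the standard error is 1/√165 = 0.078 and the interval is 0.49 to 0.69

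**The case against.** **The plan does not state a crude pooled r.** A reader might infer that one unadjusted coefficient over 183 facilities is the specified primary analysis. The text speaks only of combined data, which is compatible with a stratified or mixed model, and such detail may sit in an analysis plan that is not shown. This stands. The point therefore rests on the reason that the article gives, and the pooling effect is a risk that the wording leaves open.

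**The planned model already helps.** Transmission intensity is a named modifier, and district cross-validation compares ANC1-based prediction with prediction that does not use ANC1 data. A high pooled r would not be the only evidence. This stands in part: no country effect is named, and Zambia contributes one district, so no other sampled district in that country is available for comparison.

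**The real limit may be people per facility.** A facility at the floor of 20 first visits a month yields 60 women in the three-month window, below the 88 required per sampling unit. If Burkina Faso's 190 survey participants per district were spread over 7 facilities, each would have about 27. Take these numbers with assumed prevalence 0.30 and between-facility SD 0.10. Sampling variances are 0.21/60 = 0.0035 and 0.21/27 = 0.0078. A true r of 0.6 would then be observed as about 0.6 × √(0.01/0.0135 × 0.01/0.0178) = 0.39, and power with 21 facilities falls to about 41%. The 84% above takes 0.6 as the correlation between the observed prevalences. Also, the three countries with 21 facilities drop below 20 if two are lost. All this is plausible, but the article does not give it as the reason, and adding countries does not add people per facility.

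**Some combining is needed.** Burkina Faso, Mozambique, Nigeria and Zambia list 3, 3, 4 and 1 districts or local government areas. Country-specific district correlations are not workable there. This stands.

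**Conclusion.** The feasibility sentence contradicts Table 1. That part needs no assumption: the minimum is 20 and the country counts run from 21 to 40.

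The second part is conditional. If facilities are combined with no country term, between-country differences can produce a significant correlation without any within-country relation, even at a modest ICC: 47% of replicates at 0.2 and 91% at 0.5, with between-country correlation 0.9. A reader might go further and infer that the planning value of 0.6 would be reached by country differences alone. The documents do not support that. It becomes likely only at an ICC of about 0.7 or more with between-country correlation of 0.9 to 1.0, the article reports no ICC, and 0.6 is a planning assumption rather than a success threshold.

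This is a correction to make before analysis. It does not show that the validation would be spurious.

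**What to change.** 1. In Sample size, correct the feasibility sentence or replace it with the actual constraint, for example women or children per facility, or the number of facilities per district.
2. For the facility-level correlation, report six country-specific estimates with confidence intervals and one combined within-country estimate (country fixed effects or a Fisher-z meta-analysis), beside the crude pooled r.
3. Name country as an effect in the mixed model in Data analysis and modelling.
4. Keep the district-level correlation combined across countries, with adjustment for country.

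No new data are needed. The cost is wider intervals for single countries, most of all those with 21 facilities. The combined within-country interval is almost as narrow as the crude one if the correlation is common to all countries (0.49 to 0.69 against 0.50 to 0.69). It will be wider if the correlation differs between countries and a random-effects combination is used.
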